## Abstract

**Background:**

Persistent postconcussion symptoms (PPCSs) represent a complex phenomenon following mild traumatic brain injury (mTBI), and this phenomenon is characterized by a diverse range of symptoms that greatly impact daily functioning, including the ability to engage in physical, cognitive, and social activities. Effective rehabilitation strategies and a nuanced understanding of brain function and patient perception remain insufficiently explored in adults with PPCSs.

**Objective:**

This study aims to assess the physiological and neurofunctional effects of targeted physical exercise carried out as a graded subsymptomatic aerobic exercise program. Furthermore, the project seeks to alleviate the complex symptomatology and perception of PPCSs through the planned intervention. In addition, the study aims to obtain feedback from patients and researchers involved in this interprofessional project and to conduct a comprehensive 360-degree evaluation combining subjective and objective data in order to obtain novel insights into the symptom complexity of PPCSs, ultimately paving the way for future strategic initiatives in mTBI treatment.

**Methods:**

This randomized controlled trial enrolled 70 patients with PPCSs. The patients were randomized in a 1:1 ratio to either a control group or a training group. Patients in the control group maintained their usual activities and care. Patients in the training group underwent a 12-week tailored aerobic exercise program designed to stay below symptom-provocation thresholds, using the Buffalo Concussion Bike Test (BCBT) as the assessment instrument. The study consisted of qualitative patient interviews, physical tests, exercise evaluations, neurofunctional and structural magnetic resonance imaging (MRI) scans, and process evaluations. MRI assessed neurophysiological changes, including blood-brain barrier integrity and cerebral metabolism. The primary outcome is improvement in physical performance on the BCBT. The secondary outcomes are symptom severity, neurophysiological function, and quality of life. The study will incorporate a multimodal approach, combining subjective patient reports with objective clinical and neuroimaging data, enabling the interdisciplinary research group to perform comprehensive evaluations of the complexity of PPCSs.

**Results:**

Study funding was awarded in December 2022. Enrollment and randomization of 70 patients were completed in March 2025. The 12-week postintervention assessments concluded in August 2025. Data analysis is ongoing and expected to conclude in 2026. The results will be published in separate manuscripts in 2027.

**Conclusions:**

This study is innovative in its approach to patients with PPCSs, focusing on the effect of an individualized exercise regimen and exploring the neurofunctional underpinnings of symptom improvements as well as the patient perceptions of dealing with PPCSs. The findings are anticipated to contribute greatly to the field of PPCS management, potentially transforming current rehabilitation practices.

## Introduction

### Background

Persistent postconcussion symptoms (PPCSs) may develop in some individuals after mild traumatic brain injury (mTBI) [1,2], and mTBI can be used interchangeably with “concussion,” as defined by the American Congress of Rehabilitation Medicine in 2023 [3,4]. The symptoms represent a complex phenomenon causing a broad spectrum of issues, including musculoskeletal and balance disturbances, cognitive impairments, visual and auditory dysfunctions, fatigue, and headache-related problems [5]. Adults with PPCSs frequently demonstrate increased sensitivity to physical, cognitive, and perceptual stimuli, which can substantially impair their capacity to engage in physical activity, participate in social interactions, sustain full-time employment, and pursue or complete higher education [6].

In Denmark, approximately 30,000 to 40,000 adults experience traumatic brain injury (TBI) annually, with more than 80% of cases being classified as mTBI [6,7]. However, this number is likely underestimated owing to underreporting and the fact that only hospital contacts are included in the epidemiological statistics. Within the subset of approximately 25,000 individuals with mTBI, 40% experience symptoms persisting beyond 4 weeks, and up to 15% continue to experience symptoms up to a year or longer after the initial concussion [6]. A nationwide cohort study identified 19,732 adults aged 18‐60 years with hospital-diagnosed mTBI over 5 years from 2003 to 2007, and found that 43% of the individuals were not engaged in full-time employment 5 years after mTBI [6].

TBI involves damage to brain tissue, hemorrhage, and neurometabolic disorders [8]. In contrast, mTBI is characterized by normal imaging findings, despite the presence of complex and disabling symptoms [9]. Symptom aggravation in patients with PPCSs is unpredictable in terms of timing and severity, often impeding the ability to lead a normal everyday life. In some cases, it may even be impractical or futile to pursue basic activities. There appears to be a threshold beyond which postconcussive symptoms worsen, potentially due to intolerance to various stimuli and activities. Symptom aggravation may be caused by microtraumas in the brainstem and corpus callosum [10,11]. Symptoms of exercise intolerance are often part of the clinical presentation, and symptom-limited exercise cessation serves as an indicator of this intolerance, reflecting the underlying pathophysiology of PPCSs. Concussions are thought to disrupt autonomic nervous system regulation of cerebral blood flow (CBF), producing abnormal cardiovascular and cerebrovascular responses to increasing metabolic demands that are not detectable at rest [12,13]. A graded exercise test is capable of provoking this dysregulation in a controlled and systematic way [5,12]. By adopting the same operational definitions as Leddy et al [13] and Haider et al [14], a direct comparison with prior work using both the Buffalo Concussion Treadmill Test and the Buffalo Concussion Bike Test (BCBT) is possible.

National clinical guidelines for the nonpharmacological treatment of persistent symptoms following mTBI recommend graded aerobic physical exercise as an important part of rehabilitation; however, these guidelines also underscore the lack of evidence in the existing literature [2]. This highlights the need for further clinical controlled studies to better understand this field, including the pathophysiology of brain metabolism and blood-brain barrier (BBB) permeability [15] in association with functional ability, as well as research into patient perceptions of PPCSs.

The body of literature on PPCSs consists mainly of a limited number of randomized controlled trials (RCTs), with a disproportionate focus on the recovery of elite youth athletes following sport-related concussions [1,16-19]. This research bias significantly limits a comprehensive understanding of the manifestation of PPCSs in the general population. Furthermore, literature often overlooks the daily challenges and symptoms reported by patients in their routine lives. The evaluation of therapeutic interventions frequently lacks the integration of patient perspectives. Thus, an interdisciplinary approach that combines patient-experienced knowledge with individualized therapeutic exercise programs may provide deeper insights into postconcussion cerebral functioning. This approach has the potential to substantially advance the understanding of the field. This could lead to more informed development, implementation, and longitudinal evaluation of intervention methodologies, as well as highlight patient perceptions throughout the complex trauma of PPCSs.

The purpose of this interprofessional RCT is to investigate the effect of a 12-week graded aerobic physical exercise program combined with usual activities and/or care for the treatment of adult patients with PPCSs. Our approach provides an opportunity to triangulate subjective and objective patient data with regard to novel combinations of patient perception, physiology, and neurobiology. The overall study perspective is to establish a tailored, evidence-based active treatment for PPCSs that benefits patients and supports clinical decision-making, and to explain the pathophysiology of PPCSs.

### Objectives

This RCT evaluates the effect of an individualized graded aerobic exercise intervention in adults with PPCSs from the general population. Participants undergo an intensive battery of physical and magnetic resonance imaging (MRI) examinations, alongside personal interviews and process evaluations, throughout the intervention period. The project is divided into the following 4 subprojects:

Subproject 1: This subproject aims to understand the challenges faced by patients with PPCSs, particularly their potential intolerance to physical activity and exercise, through qualitative in-depth interviews. It is hypothesized that the interviews will reveal significant obstacles to living a normal life, with a focus on intolerance to activity and exercise.Subproject 2: This subproject aims to evaluate the efficacy of a 12-week, heart rate–controlled aerobic exercise program for patients with PPCSs. It is hypothesized that the specialized exercise program will increase the physical capacity of patients, raising the threshold of symptom provocation compared with a group of controls.Subproject 3: This subproject aims to quantify the neurofunctional aspects of PPCSs using MRI for measuring changes in brain structure and function. It is hypothesized that patients with PPCSs will exhibit increased BBB permeability, disturbances in brain metabolism, and abnormalities in brain structure and physiology compared with a group of healthy age-matched controls. The exercise intervention is expected to normalize the physiological aspects of these MRI metrics in the training group (TG).Subproject 4: This subproject aims to obtain qualitative feedback from patients and researchers on various aspects of this interprofessional scientific project, utilizing a strengths, weaknesses, opportunities, and threats (SWOT) framework. Finally, we will conduct a comprehensive 360-degree evaluation that combines subjective and objective data to attain a novel understanding of the complexity of PPCSs.

## Methods

### Trial Design

This study protocol describes the design of the Rehabilitation in Postconcussion Symptoms (REPCon) project, an assessor-blinded, parallel-group, randomized controlled superiority trial. Adult patients with PPCSs showing symptoms for more than 4 weeks after the initial mTBI were randomized in a 1:1 ratio to either a control group (CG) or a TG. Participants in both groups continued their usual daily activities and received usual care as delivered in routine clinical practice. In accordance with the pragmatic design of the trial, usual care is not standardized and reflects current real-world management. Usual care may include follow-up by a general practitioner or medical specialist, symptom monitoring, pharmacological treatment (eg, for pain or sleep disturbances), advice regarding activity modification and return to activity, and referral to allied health services such as physiotherapy or psychology, as clinically indicated. Participants allocated to the TG additionally received a supervised graded physical exercise program, as described below. Concomitant care and co-interventions were discouraged in both groups, and any changes were reported to the study group. The only protocol-mandated difference between groups was the addition of a supervised exercise intervention in the TG. The study includes the following four subprojects: (1) qualitative evaluation, (2) physiological evaluation, (3) neurofunctional evaluation, and (4) comprehensive evaluation. The primary outcome is improvement in exercise tolerance measured as time to symptom exacerbation during the graded aerobic exercise testing protocol 12 weeks after baseline [14]. The secondary outcomes include differences in symptom complexity, dynamic gait, fatigue, headache, and the findings of a range of other neurophysiological tests and functional abilities between the TG and CG at 12 weeks after baseline, as well as the normalization of quantitative MRI measures in the TG and the between-group differences in these measures. The tertiary outcome is the triangulation of data from the subprojects to provide a nuanced and integrated understanding of biology, physiology, and patient perceptions of PPCSs, thereby potentially improving clinical recommendations. The trial has been registered in the ClinicalTrials.gov repository (NCT05785000). The findings will be reported in accordance with the SPIRIT (Standard Protocol Items: Recommendations for Interventional Trials) guidelines [20,21]. The SPIRIT checklist is provided in Checklist 1.

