#### Secondary Outcomes

Secondary outcomes have been assessed as between-group differences in change scores from baseline to postintervention (at 12 weeks), unless otherwise specified.

The officially approved Danish version of the *RPQ* [22] was used to assess changes in each patient’s discomfort specifically related to concussion at both baseline and 12 weeks. Furthermore, the questionnaire was used in the TG before each training session during all 12 weeks. It is a standardized questionnaire that evaluates patient perceptions of postconcussive symptoms experienced during the previous 24 hours. Scores range from 0 (not experienced) to 4 (experienced as a severe problem) for each of the 16 items in the questionnaire, with a total score of 64 points.

The *Fatigue Severity Scale* [36] was used to assess changes in each patient’s perceived fatigue both at baseline and after 12 weeks. It is a standardized questionnaire that evaluates fatigue severity and its impact on daily functioning. Scores range from 1 (strongly disagree) to 7 (strongly agree) for each of the 9 items in the questionnaire, with a total score of 63 points.

The *Dynamic Gait Index* [37] was used to assess changes in each patient’s dynamic and functional balance during gait at both baseline and 12 weeks. It is a standardized clinical tool to evaluate how an individual responds to walking challenges. Scores range from 3 (normal performance) to 0 (severe impairment) for each of the 8 items in the index, with a maximum score of 24 points.

*BCBT changes* [14] were assessed from baseline to week 4 and from baseline to week 8. The test followed the same protocol as described for the primary outcome and was completed for re-evaluation of the exercise level in the TG.

*Physical ability* was assessed twice weekly for 12 weeks using mail or SMS text message correspondence, in which patients electronically completed a researcher-developed questionnaire on self-reported physical ability, which was inspired by a previous study [38]. The questionnaire was rated on a scale from 0 to 10, with 10 representing the best physical ability.

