$$\begin{array}{c} Y_{ij}=\beta_{0}+\beta_{1}{\text{Group}}_{i}+\beta_{2}{\text{SaO}}_{2,ij}+\beta_{3}({\text{Group}}_{i}\times {\text{SaO}}_{2,ij})\\ +\beta_{4}{\text{Age}}_{i}+\beta_{5}{\text{Sex}}_{i}+u_{i} \end{array}$$

where *Y*_*ij*_ denotes CMRO2, Group refers to either healthy controls or patients with PPCSs, and SaO2 is the actual oxygen saturation level in blood measured during the experiment (ie, during normoxia and hypoxia). Thus, we take the actual individual level of blood desaturation into account. The regression value *β*_3_ of the interaction term provides an inference regarding the patient’s ability to maintain CMRO2 under hypoxic stress conditions. After the 12-week intervention period, only patients will be tested for a possible change in their ability to maintain CMRO2 during the hypoxic exposure. Patients will be split according to group allocation (CG or TG), and the model is formulated as follows:

$$\begin{array}{c} Y_{ijk}=\beta_{0}+\beta_{1}{\text{Group}}_{i}+\beta_{2}{\text{SaO}}_{2,ijk}+\beta_{3}{\text{Time}}_{jk}\\ +\beta_{4}({\text{Group}}_{i}\times {\text{SaO}}_{2,ijk}\times {\text{Time}}_{jk})+\beta_{5}{\text{Age}}_{i}+\beta_{6}{\text{Sex}}_{i}+u_{i} \end{array}$$

where Time_ijk_ codes for pre- or postintervention (*k*) and Group codes for either the CG or TG, with the other parameters being as described above. The interaction term infers information on whether time (pre- or postintervention) has any impact on the group-specific CMRO2 response. Comparison of BBB permeability between patients with PPCSs and healthy controls will be performed using a linear regression model adjusted for age and sex, with heteroscedasticity-consistent SEs to account for possible nonconstant error variance. For exploratory regional analysis of BBB permeability across multiple brain parcels, Benjamini-Hochberg false discovery rate correction will be applied to control for multiple comparisons.

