
This study is unique because it allows us to evaluate how an intervention consisting of subsymptomatic exercise can modify the anticipated disturbed brain physiology in patients with PPCSs. Moreover, the study aims to integrate novel neuropathophysiological insights with patient perspectives on the short- and long-term impacts of PPCSs on physical, neurobiological, and social functioning.

The study has some limitations. First, patients were not blinded to group allocation, and a desire to switch to the other group could have introduced unwanted bias, leading to lower compliance and poor protocol adherence. Second, patients were required to complete 4 MRI sessions (up to 6 hours) in a noisy environment, and for some patients with PPCSs, this might be challenging and provoke an increased symptom burden. Thus, it was decided to modify the approach and consider not completing all 4 MRI sessions as acceptable. Third, patients in the TG were required to meet in person twice weekly for the 12-week aerobic exercise protocol, and this could potentially affect the primary outcome. To support participation compliance, flexible scheduling was offered. Furthermore, practical factors, such as traffic delays, canceled trains, and seasonal illnesses, might have made it difficult for patients to attend the planned sessions. Finally, participants in the TG received a higher level of supervision and clinical contact compared to those in the CG, which might have introduced a risk of attention bias.

This study is innovative in its approach to patients with PPCSs, focusing on the effect of an individualized exercise regimen and exploring the neurofunctional underpinnings of symptom improvements and the patient perceptions of dealing with PPCSs. The findings are anticipated to contribute greatly to the field of PPCS management, potentially transforming current rehabilitation practices, alleviating symptom burden, and improving recovery from mTBI.

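### Normalization of MRI measures in the training group is listed as a separate outcome; as worded it is a one-arm before/after statement that cannot be credited to exercise

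*Protocol article*

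**What the plan says.** The Trial Design section lists, among the secondary outcomes, "as well as the normalization of quantitative MRI measures in the TG and the between-group differences in these measures". The Objectives section words the hypothesis of subproject 3 for one arm: "The exercise intervention is expected to normalize the physiological aspects of these MRI metrics in the training group (TG".

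The Secondary Outcomes section sets a default: "Secondary outcomes have been assessed as between-group differences in change scores from baseline to postintervention (at 12 weeks), unless otherwise specified". It then describes oxygen consumption, diffusion, lactate and the visual-stimulation response by allocated group. BBB permeability is described both against healthy controls and by allocated group.

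For cerebral oxygen consumption (CMRO2), the Statistical Analysis section compares patients with healthy controls at baseline. After 12 weeks, "only patients will be tested for a possible change in their ability to maintain CMRO2 during the hypoxic exposure". It continues: "Patients will be split according to group allocation (CG or TG), and the model is formulated as follows". The result is read from the Group × SaO2 × Time term: "The interaction term infers information on whether time (pre- or postintervention) has any impact on the group-specific CMRO2 response". Earlier in the same section, the baseline MRI tests, which are against healthy controls, are said to be run again after 12 weeks with the intervention as a regressor. The section ends by treating the further tests as hypothesis-generating.

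**The concern.** Normalization means movement toward healthy values. An outcome that reports such movement in the TG alone is a before/after statement. The randomized control group (CG) was scanned on the same schedule so that recovery and repeat-scan effects could be subtracted, and this outcome leaves it out. The Objectives section nevertheless credits the movement to the exercise programme.

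For CMRO2 there is a second gap: the 12-week model contains patients only, so it holds no healthy value against which movement could be called normal.

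At stake is what subproject 3 may conclude. It has its own sample-size calculation, and one of the planned papers concerns whether exercise improves brain oxygen metabolism. If TG values move toward normal and the TG-CG contrast is inconclusive, the present wording would still allow the first result to be reported as a secondary outcome met.

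**Working it through.** **1. The plan's own figures.** None is given for normalization. The nearest is the BBB permeability calculation: effect size 1, significance level 1%, power 90%, 27 per group. With n = 2(z_α + z_β)²/d², a one-sided 1% test gives 2(2.326 + 1.282)² = 26.03, so 27, which matches. A two-sided test gives 2(2.576 + 1.282)² = 29.8, so 30; the article does not state the sidedness. The 70 patients give 35 per arm, and the planned 30% dropout leaves 35 × 0.7 = 24.5, about 24.

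**2. What each outcome estimates.** Let E be the exercise effect, N natural recovery over 12 weeks, and H habituation to the repeat scan, including the second hypoxic test.
- Expected change in TG = E + N + H
- Expected change in CG = N + H
- TG minus CG = E

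The TG-only outcome estimates the first line, and the between-group outcome the third. (The extra supervision in the TG, which the Discussion acknowledges, stays in both.)

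**3. Is N plausibly above zero?** The Introduction gives 40% of mild injuries with symptoms beyond 4 weeks and up to 15% at a year or longer. At least 1 − 15/40 = 62.5% of those symptomatic at 4 weeks have therefore recovered by a year, and entry opens just after 4 weeks. These are symptom figures. The article gives none for MRI measures or for a 12-week window, so the size of N is an assumption.

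**4. Size of the one-arm problem.** Assume E = 0 and recovery of g SD, pre-post correlation r, and a paired t test at two-sided 5%. Then d_z = g/√(2(1 − r)) and the noncentrality is d_z√n. The table gives the chance of a significant improvement in the TG.

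| g | r | d_z | n = 35 | n = 24 |
|---|---|---|---|---|
| 0.3 | 0.5 | 0.300 | 41% | 29% |
| 0.3 | 0.7 | 0.387 | 61% | 44% |
| 0.5 | 0.5 | 0.500 | 82% | 65% |
| 0.5 | 0.7 | 0.645 | 96% | 86% |

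With equal recovery in both arms, a correctly specified TG-CG contrast keeps its nominal 5%.

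**5. Does a healthy reference change the contrast?** With a fixed reference R, the change in distance for one patient is (R − pre) − (R − post) = post − pre. R cancels, so the TG-minus-CG difference toward R is the ordinary difference in change. R decides only whether there was a deficit to correct and whether the movement is in the right direction.

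**6. The passages on healthy controls at 12 weeks.** One paragraph of Statistical Analysis repeats the patient-versus-healthy tests after 12 weeks. The later one restricts the CMRO2 test to patients. Both cannot hold for CMRO2 as written.

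**7. A limit on the CMRO2 contrast.** The printed 12-week model has the three-way term without the two-way interactions. A simulation of 2,000 runs per setting assumed 24 or 35 per arm, random-intercept SD 1, residual SD 0.7, a hypoxic slope of −1 and an equal slope recovery of 0.3 to 0.5 in both arms. The three-way term was significant in 12% to 41% of trials, against about 5% with all two-way terms. This is a separate matter, relevant here only because the fix relies on that contrast.

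**The case against.** The strongest reply is that no one-arm analysis is specified. The listed phrase itself goes on to between-group differences, the Secondary Outcomes default is a between-group change score, the MRI measures are described by allocation, and the 12-week CMRO2 model splits patients into CG and TG. The Objectives sentence is an expectation, not a test. A numerical criterion for normal values may properly sit in an analysis plan that is not shown.

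Much of this stands. A reader might infer that the whole MRI analysis is judged in one arm; the documents do not support that. A reader might also infer that healthy controls vanish at 12 weeks. That is explicit only for CMRO2; BBB permeability keeps them, and one paragraph has the baseline tests repeated.

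A third tempting reading is that a smaller follow-up sample could by itself produce normalization, through a non-significant difference from healthy controls. The article states no such rule. At its only MRI effect size, 1.0 SD, with 24 TG patients and an assumed 27 healthy controls, that rule would call an unchanged deficit normal in about 6% of trials. The rate rises for smaller deficits, but it is not a property of this plan. Nor does the Discussion say that the most symptomatic patients are lost at week 12. It says only that "it was decided to modify the approach and consider not completing all 4 MRI sessions as acceptable", which covers baseline sessions too.

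What the reply does not remove is the outcome itself. The default applies unless otherwise specified, and Trial Design does specify otherwise by naming a TG outcome beside the between-group one. The point is not that a criterion is missing, but that the article fixes a one-arm outcome and credits it to treatment.

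**Conclusion.** The concern holds for the separate TG-only normalization outcome and its attribution to exercise, and not for the MRI analysis as a whole. As worded, that outcome mixes exercise, natural recovery and repeat-scan effects. For CMRO2 the 12-week model also offers no healthy reference.

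The 29% to 96% range in the table rests on assumed natural recovery of 0.3 to 0.5 SD in the MRI measure and a correlation of 0.5 to 0.7. With no recovery and no habituation, the TG-only test would hold its nominal level. The structural point, that the one-arm change is E + N + H, needs no assumed figure.

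Severity is minor to moderate. The randomized contrasts are already planned and the further tests are labelled hypothesis-generating, so what is at risk is the claim subproject 3 may make, not the primary result.

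**What to change.** - In Objectives and Trial Design, replace the TG-only outcome with the TG-minus-CG difference in change for each MRI measure.
- Call a result normalization only where patients differ from healthy controls at baseline and the change is toward the healthy-control value, taken from the existing baseline scans and adjusted for age and sex.
- Show the week-12 distance of TG and CG from that reference, with confidence intervals.
- State that a change seen in the TG alone will not be credited to exercise.
- Make the two paragraphs of Statistical Analysis agree on the role of healthy controls at 12 weeks.
- Where the CMRO2 contrast carries the claim, fit it with the two-way interactions included.

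The cost is wording in the outcome list and the analysis plan; no new scans are needed. Because the reference cancels out of the contrast, the gain lies in which claim is permitted, not in a new estimate. The downside is that an improvement confined to a TG before/after comparison can no longer be reported as an exercise effect.
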